### Sample size

The study is an effectiveness trial and will use intention-to-treat analysis. Based on the primary outcome of maternal weight status at 12 months postpartum, to detect a 0.8-kg/m^2^ BMI difference between the groups with a standard deviation of 2 kg/m^2^ BMI, a type I error rate of 5%, and to achieve 80% power, 800 women need to be recruited to the trial (i.e. 400 in each arm of the study). This incorporates an assumed retention rate of 70% which is more conservative than previous studies to allow for country-level variance in retention. Each site will recruit 200 women over a 12-month period. Based on previous experience recruiting women from this setting and examining the potential numbers of eligible women using the current Monash Health rate of women scoring 3 or higher on the GDM screening tool (estimated to be approximately 33% prevalence), it is anticipated that recruitment will take around 12 months.

The study flow is described in Fig. 1.

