Baseline characteristics will be compared between the intervention and control groups using the *χ*^2^ tests, the independent *t*-tests, and/or the Wilcoxon rank-sum test, as appropriate. Primary and secondary outcomes will be evaluated using repeated-measures analysis of variance (ANOVA) or mixed model analyses. Two-sided tests will be used, with a level of *P* < 0.05 determining statistical significance. Comparisons of the assessment times (the baseline and 12 months postpartum differences) within each treatment group (control or intervention) will be based on *t*-tests that utilise the standard errors of the differences that are computed as part of the repeated-measures analysis. Covariates included in the model will be kept to a minimum—site is the only covariate expected. The impact of loss to follow-up will be minimised by using a marginal model, which is not subject to list-wise deletion: each participant will contribute all time-specific measurements made to the model. Missing data will be reported for each outcome and handled by applying multiple imputation methods [60]. Subgroup analyses will be carried out to investigate the site differences based on the substantial demographic and operative differences in the four clinical sites. There are no interim analyses planned. Analyses will be conducted using the IBM SPSS software (version 26.0 or later; IBM), STATA version 12 or later (Stata Corp., College Station, TX, USA), or SAS software (SAS Institute Inc., Cary, NC, USA), as appropriate for analysis type. Data analysts will be blinded to group assignments.

A statistical analysis plan and data management plan have been prepared for the project which outlines plans for data entry, coding, confidentiality, security, and analysis in line with best practice (Additional file 2). Each clinical site is incorporated in this data management plan and provided the details to their relevant ethics committee. The project has an independent data manager who oversees the data monitoring and analyses and reports back to the RCT Working Group. There is no formal data monitoring committee; however, the external advisory board receives reports from the data manager.

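### The planned 800 women do not follow from the stated inputs: a 0.8 kg/m² difference, SD 2, 80% power and 70% retention require about 286

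*Protocol article*

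**What the plan says.** The Sample size section of the protocol article gives the whole calculation for BMI at 12 months postpartum. The aim is "to detect a 0.8-kg/m^2^ BMI difference between the groups", "with a standard deviation of 2 kg/m^2^ BMI", and the conclusion is "a type I error rate of 5%, and to achieve 80% power, 800 women need to be recruited to the trial", that is, 400 per arm. On loss to follow-up it says "This incorporates an assumed retention rate of 70" per cent, so the 800 is meant to include that allowance. The same section plans 200 women at each site.

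Two other sections complete the inputs. Randomisation procedure specifies individual 1:1 allocation within sites. Statistical analyses says "Two-sided tests will be used" and expects site to be the only covariate. The article mentions no design effect, no power target within sites, no multiplicity adjustment and no powering on another outcome.

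**The concern.** Every quantity needed to recompute the total is printed, and the total is far from what those quantities give. A gap of 2.8-fold is too large for rounding or for the choice between normal and t formulas.

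This paragraph is the only power justification in the article for the primary outcome. As it stands, the stated 80% is not the power implied by the stated difference, SD and number retained. At least one printed element is therefore not what was used, or something that raised the total was left out. A reader cannot tell which, and so cannot tell what effect the trial was sized to detect.

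**Working it through.** **Inputs.** From Sample size: difference δ = 0.8 kg/m², SD σ = 2 kg/m², type I error 5%, power 80%, retention 70%, total 800 (400 per arm). From Statistical analyses: two-sided tests. From Randomisation procedure: 1:1 allocation.

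**1. Attempt to reproduce 800.** Analysed women per arm:

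n = 2(z₀.₉₇₅ + z₀.₈₀)² σ²/δ² = 2 × (1.960 + 0.842)² × 4/0.64 = 98.1, so 99.

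The exact t-test calculation gives 99.08, so 100. Allowing for retention, 100/0.70 = 142.9, so 143 per arm and 286 in total (99/0.70 gives 142 per arm and 284 in total). The stated total is not reproduced: 800/286 = 2.8.

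**2. Power that the stated inputs give.** Retained per arm: 400 × 0.70 = 280. Standard error of the difference: 2 × √(2/280) = 0.169. Then 0.8/0.169 = 4.73, and power = Φ(4.73 − 1.96) = Φ(2.77) = 99.7%.

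**3. Difference detectable with 80% power at SD 2.** (1.960 + 0.842) × 0.169 = 0.47 kg/m².

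**4. Other conventions.** With δ = 0.8 and SD 2 (normal approximation):

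| Variant | Total recruited |
|---|---|
| One-sided, 80% power | 224 |
| Two-sided, 90% power | 378 |
| Two-sided, 95% power | 466 |
| Two-sided, 99% power | 658 |
| Two-sided, 80%, variance doubled | 564 |
| Two-sided, 80%, inflated by 1.3 instead of divided by 0.7 | 258 |

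None gives 800.

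**5. What would give 800.**

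- With the retention allowance kept (280 per arm), 80% power for 0.8 kg/m² requires σ = 0.8/(2.802 × √(2/280)) = 3.38.
- With SD 2 and the allowance kept, a design effect of 280/100 = 2.8 would be needed.
- With the allowance dropped (400 per arm analysed), the SD would be about 4.0.
- Four sites each powered alone need about 4 × 200 = 800 (4 × 198 = 792 by the normal formula), again with the allowance dropped. With it kept, the total is 4 × 2 × 142 = 1,136. Within one site, 100 per arm gives 80.4% power and 70 per arm gives 65.2% (t-test).

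Each route either contradicts a printed input or needs an element that the article does not state.

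**The case against.** The strongest reply is that the error, if it is one, is on the safe side: on the printed inputs, 800 exceeds the requirement and power is above 80%. That stands. Nothing stated puts the type I error, the analysis or recruitment at risk.

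A second reply is that a site-based total is plausible. The design has 200 women per site, blocks of 200 per site, and planned subgroup analyses by site because the sites differ. That also stands as a possible explanation, but it does not rescue the paragraph. The article does not state this basis, and it reaches 800 only without the loss to follow-up that the text says is included.

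A third reply is that 99.7% assumes independent observations. Two coaches at each of four sites would have about 280/8 = 35 retained intervention women each. With an assumed within-coach correlation of 0.01 to 0.05 (not in the documents), the variance in that arm is multiplied by 1 + 34 × 0.01 = 1.34 to 1 + 34 × 0.05 = 2.70, and power for 0.8 kg/m² falls to about 99% to 94%. The 99.7% should therefore carry that condition. Averaged over both arms, the larger value is (2.70 + 1)/2 = 1.85, so these correlations do not account for a factor of 2.8.

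A last reply is that the type and source of the SD belong in the full protocol or analysis plan. That is accepted. The point is only that the printed result does not follow from the printed inputs, which no other document can change.

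**Conclusion.** The stated figure is wrong as written. On the printed inputs, 80% power needs about 100 analysed women per arm and about 286 recruited, not 800. The 800 recruited would give about 99.7% power for 0.8 kg/m², or 80% power for about 0.47 kg/m². These figures assume a two-sided two-sample comparison, independent observations and 280 retained per arm.

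The documents do not support several stronger readings that a reader might infer:

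- **That the SD or the power is the wrong element.** The cause is not shown. The difference, the retention allowance, an unstated design effect or a per-site basis are also possible.
- **That the trial is underpowered.** After 30% loss, this requires an SD above about 3.4, and the article gives no SD other than 2.
- **That trivial differences will be declared significant.** At SD 2 the significance threshold is an observed difference of about 0.33 kg/m² (1.96 × 0.169), but nothing in the article calls that size trivial.
- **That the result could not be interpreted.** The 0.8 kg/m² target is fixed, and a confidence interval can be read against it whatever total was planned.

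**What to change.** Keep 800 and restate in the Sample size section the calculation actually used, so that difference, SD, power, retention and total agree. One of three forms will fit:

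- (a) If SD 2 is right, state about 99.7% power for 0.8 kg/m², or 80% power for about 0.47 kg/m², with 560 completers and assuming independent observations.
- (b) If another SD or a design effect was used, give it. At 70% retention and 80% power this would be an SD of about 3.4 or, with SD 2, a design effect of about 2.8.
- (c) If the total was set for power within each site, say so and give the within-site power after 30% loss, about 65% at 70 women per arm with SD 2.

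The cost is rewording one paragraph. Recruitment and analysis do not change.

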### Intervention

The intervention group will receive mHealth coaching support from enrolment in the study until 1 year postpartum. The mHealth coaching will be delivered by trained health coaches with a healthcare professional background including nutrition, nursing, physiotherapy, or health psychology. The coaches will drive the woman’s engagement with the app content and personalise their behaviour change experience based on their own goals and needs. The smartphone app content and the health coach training programme are based on previous research from RCTs which were effective at reducing unhealthy weight gain in both the mother and child [16, 17, 27]. The intervention incorporates content from the PEARs and MADGA RCTs which were effective in reducing maternal weight gain in pregnancy and postnatally respectively and My Baby Now study which is based on the InFANT program RCT, effective in influencing child obesity risk behaviours [27, 29]. Each intervention was designed using behaviour change theory; the Behaviour Change Wheel theoretical framework was overlaid onto the app development to ensure complete and cohesive coverage of techniques [30]. The app and health coach environment are supported by a developed and tested commercial platform that uses a health coach dashboard to coordinate and tailor engagement at the individual level. The platform will integrate seamlessly with a woman’s smartphone, and two local health coaches will deliver the intervention at each site. A summary of the components and frequency is detailed in Fig. 3.

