**Methods:**

Eight hundred women will be recruited in early pregnancy from 4 clinical sites within Ireland, the UK, Spain, and Australia. Women will be screened for eligibility using the validated Monash GDM screening tool. Participants will be enrolled from 12 to 24 weeks’ gestation and randomised on a 1:1 basis into the intervention or control arm. Alongside usual care, the intervention involves mHealth coaching via a smartphone application, which uses a combination of synchronous and asynchronous video and text messaging, and allows for personalised support and goal setting with a trained health coach. The control arm receives usual care. All women and their children will be followed from early pregnancy until 12 months postpartum. The primary outcome will be a difference in maternal body mass index (BMI) of 0.8 kg/m^2^ at 12 months postpartum. Secondary maternal and infant outcomes include the development of GDM, gestational weight gain, pregnancy outcomes, improvements in diet, physical activity, sleep, and neonatal weight and infant growth patterns. The 5-year project is funded by the EU Commission Horizon 2020 and the Australian National Health and Medical Research Council. Ethical approval has been received.

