## Methods

### Study design and setting

Bump2Baby and Me is a multicentre single-blind randomised controlled trial involving 800 pregnant women to investigate an mHealth coaching programme for those who are at high risk of developing GDM. This study involves five hospital sites across four countries: National Maternity Hospital in Dublin, Ireland; Clinical University Hospital San Cecilio and Mother-Infant University Hospital in Granada, Spain; Southmead North Bristol NHS Trust in Bristol, England; and Monash Medical Centre in Melbourne, Australia. Ethical approval has been granted for all study sites. This RCT was registered prospectively on the Australian New Zealand Clinical Trials Registry, trial registration number ACTRN12620001240932, on 19 November 2020. The study flow design is described in Fig. 1.

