**Fig. 3 Fig3:**
[figure not shown]
Summary of the Bump2Baby and Me intervention components and frequency of each in the app

The intervention consists of six components as follows:
Synchronous mHealth coaching: Coaching sessions are conducted on a 1:1 basis between the mHealth coach and participants. There will be 2 synchronous sessions, the first at enrolment and the second between 4 and 8 weeks postpartum. These sessions will last 45–50 min with a follow-up summary video message of the goals discussed and, at the first session, the establishment of a behaviour change agreement. These sessions are mediated through a live-video feature in the mHealth coaching app. If the woman is diagnosed with GDM, there will be an opportunity for a third 15-min synchronous coaching session to review and adjust any lifestyle goals to align with the individual’s diabetes in the pregnancy management plan.Asynchronous mHealth coaching: This uses a combination of text and video messaging exchanges between the mHealth coach and participant and tailored to the woman’s needs. The pregnancy interactions will be once a week for the first 4 weeks. The mHealth coaching then becomes bi-weekly for 2 months and then monthly until birth. The postpartum interactions will be after the second synchronous coaching session. These will happen bi-weekly for 1 month, to support the woman to ease back into mHealth coaching contact after the birth. After that, it will be weekly for a month, then bi-weekly for a month prior to monthly check-ins with the mHealth coach. However, this will be arranged with the woman during the postpartum synchronous coaching session and will be adapted accordingly. From 6 to 12 months postpartum, asynchronous coaching will happen monthly.Automated push notifications: These will include messages prompting the individual to follow through on the goals they have set for themselves, reminders to register goal achievements, and motivational messages when they have accomplished their goals. Whilst these are standardised messages, their frequency of delivery will be tailored to match the individual’s goals. For example, if a woman sets a weekly goal to exercise, they will receive a weekly push reminder about this goal.Personalised educational content: Provided by the mHealth coach during the asynchronous coaching sessions, this content will cover topics within navigating the healthcare system and antenatal appointments, healthy eating for pregnancy and postpartum, physical activity, emotional well-being, breastfeeding, and best practice formula feeding. Each mHealth coach will continuously assess what content is relevant before sending it to the women.Additional support content: Participants will also receive automated push notifications referring to additional content available in the app. The content push notifications will be active once a week during the weeks that no asynchronous mHealth coaching occurs. These push notifications will connect participants with specially designed online resources providing tailored information such as recipes, tips for food and activity choices, breastfeeding resources, and links to relevant support agencies.Virtual social network: Participants will have access through the mHealth coaching app to a network with other women participating in the intervention arm of the study where messages can be sent. This will enable social engagement and support, as well as the capacity to connect physically for shared activities, self-organised in each study site.

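### Two coaches per site deliver the intervention arm only, but the stated model has no coach term; if the coach ICC is 0.01 to 0.05, two-sided type I error is about 7% to 15%

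*Protocol article*

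**What the plan says.** **Delivery.** The Intervention section says that "two local health coaches will deliver the intervention at each site". In its list of components, "Coaching sessions are conducted on a 1:1 basis between the mHealth coach and participants", and the asynchronous messages and educational content also come from the coach. The Control section describes written information and websites, with no coach.

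**Numbers.** The abstract says "Eight hundred women will be recruited in early pregnancy from 4 clinical sites within Ireland, the UK, Spain, and Australia". The Sample size section adds "Each site will recruit 200 women over a 12-month period", with 400 women per arm and 70% retention. Study design and setting says "This study involves five hospital sites across four countries". The sample size inputs are a difference of 0.8 kg/m², SD 2 kg/m², 5% type I error and 80% power. No ICC or design effect is among them.

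**Analysis.** Statistical analyses plans repeated-measures ANOVA or mixed models, with two-sided tests at 5%. It says "Covariates included in the model will be kept to a minimum—site is the only covariate expected". A marginal model is introduced to deal with loss to follow-up. The article names coach neither as a random effect nor as a unit of clustering.

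**The concern.** If coaches differ in how much they help, women who share a coach have correlated 12-month BMI. This happens only in the intervention arm, which makes the design partially nested. A model with site alone removes what both arms of a site share. It does not remove a coach effect that acts on the intervention women and not on the controls at that site. Analysed as independent women, the intervention mean looks more precise than it is. The confidence interval for the primary comparison is then too narrow and its P value too small.

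The target of inference makes this matter. The Background and Discussion aim at a programme that routine services can adopt, which means delivery by coaches other than those in the trial. For that claim, variation between coaches belongs in the error term. The article itself treats delivery as variable: coaches come from several professions, and a fidelity index is to be related to participant outcomes.

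**Working it through.** **Inputs from the article.** Four recruiting sites of 200 women, 1:1 allocation, two coaches per site, 70% retention, SD 2, difference 0.8.

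- Intervention women per site: 200/2 = 100, so 50 per coach randomised and 50 × 0.7 = 35 analysed.
- Analysed per arm: 400 × 0.7 = 280, which is 8 coaches × 35. With five hospitals and a pair at each, it is 10 coaches × 28.

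**Assumed inputs.** The coach ICC is not in the article; the range is 0 to 0.05. Each woman is taken to have one main coach, with equal caseloads.

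**The plan's own figure.** n per arm = 2 × (1.96 + 0.842)² × 2²/0.8² = 98.1, so 99; 99/0.7 gives 142 per arm and 284 in total, not 800. That mismatch is a separate point. It matters here in two ways: no stated design effect explains the surplus, and a larger sample does not protect the type I error of a model that omits coach.

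**Standard error and type I error.** With independence, SE = 2 × √(2/280) = 0.169. With coach clusters of size m in one arm only, the variance of the difference is multiplied by

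R = [(1 + (m − 1) × ICC) + 1]/2 = 1 + (m − 1) × ICC/2.

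The actual two-sided error of a nominal 5% test that ignores coach is 2 × [1 − Φ(1.96/√R)]. It does not depend on the SD.

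| ICC | R (m = 35) | SE ratio √R | True SE | Type I error, 8 coaches | Simulated | Type I error, 10 coaches of 28 |
|---|---|---|---|---|---|---|
| 0 | 1.00 | 1.00 | 0.169 | 5.0% | 5.0% | 5.0% |
| 0.005 | 1.085 | 1.04 | 0.176 | 6.0% | not run | 5.8% |
| 0.01 | 1.17 | 1.08 | 0.183 | 7.0% | 7.2% | 6.6% |
| 0.02 | 1.34 | 1.16 | 0.196 | 9.0% | 9.4% | 8.2% |
| 0.05 | 1.85 | 1.36 | 0.230 | 15.0% | 15.1% | 13.0% |

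The simulation used 20,000 trials per ICC: 4 sites, 2 coaches of 35 and 70 controls per site, and a linear model with site and arm. The model's average SE stayed near 0.169 at every ICC. The actual spread of the estimate rose to 0.183, 0.197 and 0.230. Site adjustment therefore does not remove the problem.

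**Power if coach is modelled** (difference 0.8, SD 2, 8 coaches, noncentral t with the true SE above). Coaches within sites give 8 − 4 = 4 df. A Satterthwaite calculation combines them with the controls' 279 df. In units of 4/280, the intervention variance is 1 + 34 × ICC and the control variance is 1, so

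df = (2 + 34 × ICC)² / [(1 + 34 × ICC)²/4 + 1/279].

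- ICC 0.01: 2.34²/(1.34²/4 + 0.0036) = 12.1
- ICC 0.02: 2.68²/(1.68²/4 + 0.0036) = 10.1
- ICC 0.05: 3.70²/(2.70²/4 + 0.0036) = 7.5

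| ICC | Power on 7 df | Power on strict 4 df |
|---|---|---|
| 0.01 | 96% | 90% |
| 0.02 | 94% | 86% |
| 0.05 | 85% | 74% |

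**The case against.** **The analysis plan may cover it.** The article says that a statistical analysis plan exists, and it is not shown. A random coach effect is not strictly a covariate, and the sentence on covariates is hedged. A reader might infer that the trial will certainly ignore coaches; the article does not show that. It does commit to a model description and a sample size, and neither contains coach. The marginal model is there for each woman's repeated measurements, not for correlation between women.

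**No ICC is given.** A reader might also infer that type I error does exceed 5%. The documents do not support that. At ICC 0 it is 5%, and at 0.005 about 6%. If coaching does nothing through any coach, there is no coach variance. The excess arises when the average effect is zero but coaches differ. This stands, and the claim must be conditional.

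**The top of the range is demanding.** At SD 2, ICC 0.05 means a coach SD of 2 × √0.05 = 0.45 kg/m². With a zero mean, 95% of coach effects would lie within ±0.88, wider than the 0.8 target itself. ICC 0.01 gives a coach SD of 0.20 and ±0.39. The 15% figure is an upper bound of the assumed range and not an expectation. The coaching manual, continuing fidelity feedback and standardised notifications should limit coach variation. Tailoring to each woman's own goals does not by itself make women of one coach alike.

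**Assignment is assumed.** The article does not say that each woman keeps one coach. If a site's two coaches share women, the nesting is looser than calculated.

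**The social network adds nothing.** Intervention women can also join "a network with other women participating in the intervention arm of the study where messages can be sent". This is organised by site, not by coach, and is not evidence of coach clustering.

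**Inference limited to these coaches** is a possible choice, but it fits poorly with the stated aim of wider implementation.

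**Conclusion.** The point holds in conditional form. The structure is in the text: a few coaches, individual coaching in one arm only, and a stated model and sample size that leave coach out. For any positive coach ICC, that model understates the standard error, so the direction is certain once coaches differ. The size is not known. The range of about 7% to 15% rests on an assumed ICC of 0.01 to 0.05, 8 coaches, one main coach per woman and 35 analysed women each; ten coaches narrow it to 6.6% to 13%. This should be changed because the remedy is concrete and inexpensive, but it is not evidence that the trial's result will be wrong. The power figures depend on the planned SD of 2 and would be lower with a larger SD.

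**What to change.** 1. Record the main coach for each intervention woman, and note changes or sharing of coaches. The article says that coaching interactions are recorded, so coach identity is probably recoverable, although it does not state that a coach identifier is held.
2. Fit the primary comparison as a partially nested mixed model: site as a fixed effect, a coach random effect in the intervention arm only, residual variance by arm, and Satterthwaite or Kenward-Roger degrees of freedom. At minimum, prespecify this as a sensitivity analysis. If the analysis plan already does so, the article should say so.
3. Report the coach ICC with its interval, and state an assumed value in the sample size section.

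**Cost.** One variable and a few lines of code. The confidence interval is somewhat wider and the degrees of freedom are fewer. Power for 0.8 at SD 2 stays at roughly 85% or more on about 7 df; the exception is ICC 0.05 on a strict 4 df, where it is about 74%. With so few coaches the ICC itself will be imprecise. The article plans blinded data analysts, and a coach code that exists in one arm only reveals allocation. Blinding can be kept by running prewritten code, or by adding coach codes after the main model is locked.
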